**Secondary Outcome Measures:**

- Reduction in low birth weight in newborns
- Mean change in weight-for-height z-score (WHZ).
- Improvement in infant and young child feeding (IYCF) indicators.
- Linear growth velocity (HAZ increment/month).
- Mean hemoglobin concentration in children 6-23 months and 24-59 months of age.
- Prevalence of childhood anemia (Hb concentration<11g/dL) in children 6-23 months and 24-59 months of age.
- Mean hemoglobin concentration in mothers.
- Prevalence of maternal anemia (Hb concentration<12g/dL).
- Maternal BMI
- The change in BMI z-score over the intervention period

To calculate HAZ, WHZ and WAZ scores the 2006 WHO growth reference will be used. Hemocue machines will be used to measure Hb concentration.

**Reporting**

The project supervisor and data management unit will generate fortnightly indicator report for anthropometry and other process indicators. These reports will be shared with all stake holders.

**Plan of operations**

To ensure that various activities will be undertaken within the scheduled time for fieldwork, a comprehensive plan of operations will be planned as follows:

- Identification of resources
- Dialogue with the community elders / representatives
- Planning of field activities
- Questionnaire design and pre-testing
- Recruitment of field staff
- Training of field staff
- Mapping and selection of household
- Data collection & anthropometry measurements
- Data entry and cleaning
- Data analysis & reporting

**Quality Assurance**

To ensure proper implementation of study activities, the project supervisor will make spot checks and will give feedback to data collectors. In addition, 2-5% households will be re-interviewed within 24 hours of the original interview. For, objectivity, the staff involved in the monitoring will be totally independent of other project staff and will be specifically trained in interviewing and anthropometry assessments. Standard quality checks will be strictly enforced for anthropometric measurements.

**Data Management:**

**Editing, Coding and Data Transferring**

Data collection will be recorded on paper questionnaires. All interviews will be conducted in Sindhi. All collected data will be cross-checked by field supervisors after the data collection on a daily basis and will be transferred to the Data Management Unit prior to data entry, all forms will be checked for completeness and consistency. In case of inconsistency or missing responses, the editors will flag the errors/omissions and consult the data collectors for possible explanations.

**Data Entry and Data Quality Assurance**

All data will be double entered for purpose of sufficient accuracy. Data quality will be assured by performing dual and error checks simultaneously during entry.

**Software**

Visual Fox Pro will be used for designing of databases, data entry software and procedures for data quality assurance. Data entry screens will employ range and consistency checks and skips to minimize entry of erroneous data. Special arrangements will be made to enforce referential integrity of the database so that all data tables are related to each other without problem. Analysis of data will be done through SPSS version 18. The anthropometric data will be managed through the WHO Anthro software however for the day to day monitoring and quality assurance of data ENA SMART software will be used.

**Data Analysis**

For data analysis SPSS version 18 will be used and data will be analysed using univariate and multivariate methods. Statistical Analysis will be performed after the availability of clean and quality data. Each file will be converted from Fox Pro into SPSS files so that they could be read into SPSS for further analysis. Descriptive statistics for the subjects will be obtained and Pearson Chi square test will be used to establish association between categorical variables. Simple frequency tables will be generated to ascertain the information on Socio-economic and demographic data. Bivariate analysis will be done to establish association with the various factors and growth parameters such as stunting, wasting and underweight. Data analysis will be conducted based on the agreed dummy tables.

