**Methodology and Study Design:**

The effectiveness of the project will be measured in terms of the impact of the proposed interventions on the stunting and micronutrient deficiency prevalences in the target group (children and mothers). Given the conditions of project implementation, a quasi-experimental “double difference” design would be appropriate to assess the impact of the intervention. We propose to compare the intervention and non-intervention (control) groups before (first difference) and after the intervention (second difference).

Then, the operational implementation of the research comprises a baseline and end line surveys. In addition, a nested cluster randomized controlled trial will be implemented to track the evolution of key variables related to the quality of intervention delivery and intermediate nutrition outcomes. The control clusters will receive routine public and private health services available in the area. The overall research design is shown in Figure 1.

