**Figure 1: Overall research design**

[figure not shown]

To ensure the robustness of this program a baseline and endline surveyswith a nested cluster randomized control trial to evaluate the programme in terms of nutrition and other core indicators is required. Therefore Division of Women & Child Health Aga Khan University proposes two separate cross sectional surveys which will be conducted in the target union councils of District Thatta-Sajawal to address the objectives of impact assessment of stunting prevention project. A baseline cross sectional survey will be conducted to provide benchmark indicators and frame work for the implementation of program. A structured questionnaire will be used to accomplish this information. At the end of the program an end line cross sectional survey will be conducted to assess the impact of the program, where the nutrition and other core indicators will be compared for pre and post intervention change.

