**Methodology for Cluster Randomized Controlled Trial**

**Sample Size Estimation:**

A union council has been taken as the cluster for the estimation of sample size for RCT. The following three sample sizes were calculated to detect a range of differences in nutritional status for all study participants;

1. Pregnant and Lactating Women: To calculate sample size for PLW, we aimed to achieve a 25% difference in the prevalence of low birthweight. With a power of 0.80 and a statistical significance of 0.05, we calculated that a sample size of 160-170 per cluster would be sufficient for analyzing the reduction in low birthweight. A total of 2,000 PLW will be enrolled in the trial.
2. Children 6-23 months: Sample size for children aged 6-23 months was calculated to detect a 10% difference in risk reduction in stunting among the intervention group compared to the control group. A sample size of 70-75 children per cluster was estimated with a statistical significance of 0.05, power of 0.80, and an intra-cluster correlation of 0.02. A total of 900 children, 6-23 months old will be enrolled in the trial.
3. Children 24-59 months: To detect a 10% difference in risk reduction in stunting among the intervention group compared to the control group, a sample size of 90-95 children per cluster was drawn, with a statistical significance of 0.05, power of 0.80, and an intracluster correlation of 0.02. A total of 1100 children aged 24-59 months will be enrolled in the trial.

The total sample size will be taken from 12 union councils which will be randomly selected from the list of 29 union councils, 6 union councils for intervention group and 6 union councils for control group.

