**Outcome Measures:**

**Primary Outcome Measure:**

The primary outcome will be reduction in risk of stunting in intervention group compared with control group.

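### The only inferential test the protocol names ignores clustering: used for the trial's stunting comparison it would give about 21% to 24% false positives at ICC 0.02, and it cannot give the planned double difference

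*Protocol*

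**What the plan says.** Data Analysis closes part B of the protocol, the part on the nested cluster randomised trial. It states that "data will be analysed using univariate and multivariate methods" and that "Pearson Chi square test will be used to establish association between categorical variables". It adds bivariate analysis of factors against stunting, wasting and underweight, and refers to agreed dummy tables. It does not mention clusters, survey design or a group-by-time term, and it does not separate the trial analysis from the survey analysis.

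The design sections do recognise clustering:

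- Trial (Sample Size Estimation): "A union council has been taken as the cluster for the estimation of sample size for RCT". Allocation is "6 union councils for intervention group and 6 union councils for control group". For the younger cohort, "A sample size of 70-75 children per cluster was estimated with a statistical significance of 0.05, power of 0.80, and an intra-cluster correlation of 0.02"; the older cohort uses the same ICC with 90-95 children per cluster.
- Surveys (Sample size and design for Baseline and End line Surveys): two-stage cluster sampling, a design effect of 1.5, and Lady Health Worker (LHW) catchment areas as the clusters.
- Primary Outcome Measure: "The primary outcome will be reduction in risk of stunting in intervention group compared with control group".
- Methodology and Study Design, on the surveys: "We propose to compare the intervention and non-intervention (control) groups before (first difference) and after the intervention (second difference)".

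**The concern.** The primary outcome is binary and is compared between two arms, so it is an association between two categorical variables. Followed literally, the Data Analysis section tests it with a chi-square on individual children. Children in one union council resemble each other, and the protocol quantifies this when it sets the sample size. A test that then ignores it understates the variance, so chance differences between union councils are declared effects too often. The protocol means these results to guide scale-up and integration into health programmes.

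The second problem is the quantity estimated. The surveys are designed around a contrast of changes between groups. A chi-square tests association in a two-way table; it returns neither the difference in changes nor an interval for it.

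**Working it through.** **Inputs (protocol).** Trial: 12 union councils, six per arm; ICC 0.02; totals of 900 and 1100 children; significance level 0.05 (sidedness is not stated; two-sided assumed). Surveys: design effect 1.5.

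**Cluster sizes.** 900/12 = 75 and 1100/12 = 91.7, which agree with the stated 70-75 and 90-95. The stated 80% power could not be reproduced. The trial section gives no control rate; borrowing 49% from the survey section, a 10-point fall needs 386 effective children per arm, while six clusters at ICC 0.02 can never supply more than 6/0.02 = 300. That is a separate matter and does not enter the calculation below.

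**Design effect.** DEFF = 1 + (m - 1) x ICC.

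- 6-23 months: 1 + 74 x 0.02 = 2.48.
- 24-59 months: 1 + 90.7 x 0.02 = 2.81.

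**False-positive rate of an unadjusted test.** Under no effect, the chi-square's underlying z statistic has variance DEFF instead of 1, so the true rate is 2 x [1 - Phi(1.96/sqrt(DEFF))].

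| Comparison | DEFF | 1.96/sqrt(DEFF) | True rate |
|---|---|---|---|
| Trial, 6-23 months | 2.48 | 1.245 | 21.3% |
| Trial, 24-59 months | 2.81 | 1.169 | 24.3% |
| Survey, simple two-group comparison | 1.50 | 1.600 | 11.0% |

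Across the quoted cluster sizes of 70 to 95, the trial rate runs from 20.4% (DEFF 2.38) to 24.8% (DEFF 2.88).

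**Simulation.** Beta-binomial data, six clusters per arm, no effect, assumed prevalence 49%, 200,000 replicates:

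| ICC | m = 75 | m = 92 |
|---|---|---|
| 0.01 | 13.6% | 15.6% |
| 0.02 | 21.2% | 24.6% |
| 0.05 | 36.6% | 40.8% |

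At ICC 0.02 the simulation agrees with the formula. Prevalence matters little: 44% with m = 75 gives 21.2% again.

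**A valid alternative on the same data.** In a separate simulation of 20,000 runs at ICC 0.02, a t-test on the 12 union-council proportions rejected in 5.0% (75 per cluster) and 4.9% (92 per cluster).

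**Double difference.** The planned quantity is (intervention endline - intervention baseline) - (control endline - control baseline). It needs four prevalences and an interaction of group with round. A chi-square of group by stunting at one round, or of round by stunting in one group, uses only two of the four.

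**The case against.** The best defence is that the section never assigns the chi-square to the primary comparison. The test shares a sentence with descriptive statistics, the bivariate work may be about risk factors, and the unspecified multivariate methods could include a clustered model or an interaction. A statistical analysis plan, not seen here, may give the details. A reader might therefore infer from this point that the chi-square is the settled primary analysis. The protocol does not say so, and the 21-24% arises only if the plain test is used for that comparison. What remains is that the section names an unsuitable test without limiting its use, in the part of the protocol about the trial. An analysis plan that used a clustered method for the arm comparison would sit at odds with that unrestricted sentence.

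Three further inferences go too far:

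- **That 21-24% also applies to the surveys.** Their stated design effect gives about 11%, and that is approximate. Under Study site, both survey groups lie in the same 29 union councils, so shared variation may partly cancel, and the planned contrast is a double difference.
- **That the protocol has fallen back on an uncontrolled before-after test.** The text after Figure 1 says that "nutrition and other core indicators will be compared for pre and post intervention change", and the cost-effectiveness section takes its effect from a before-after survey. But Methodology and Study Design states the controlled comparison, and endline subjects are drawn from both areas. The loose wording does not show that the control group was dropped.
- **That a figure can be given for low birth weight.** That sample-size calculation states no ICC. With 167 women per cluster, assumed values of 0.005 to 0.02 give about 15% to 35%; no point estimate is claimed.

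**Conclusion.** The point holds in conditional form. The only named inferential test ignores the clustering on which both sample sizes were built. Used for the trial's stunting comparison, it turns a nominal 5% into about 21% (6-23 months) and 24% (24-59 months), four to five times the intended rate. This rests on the protocol's own ICC of 0.02, equal cluster sizes and a two-sided test. Over an assumed ICC range of 0.01 to 0.05, the rate stays well above 5%, at roughly 14% to 41%. For a simple two-group survey comparison the rate is about 11%. Whatever the ICC, the chi-square does not produce the double difference. Because the wording concerns the primary outcome and is cheap to correct, it should be corrected before analysis.

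**What to change.** Amend Data Analysis as follows:

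1. Limit the Pearson chi-square to descriptive tables.
2. For the trial, compare arms by a cluster-level analysis of the 12 union-council summaries (t-test or regression, 12 - 2 = 10 degrees of freedom before any covariates), or by a mixed or GEE model with the union council as cluster and a small-sample correction.
3. For the surveys, fit a regression with arm, round and arm x round, and report the interaction as the effect. Use design-based standard errors that respect the LHW catchment clusters given in the survey sampling section, and the union council as the higher-level unit where applicable.

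The cost is a few sentences and modest analysis work. The downside is wider, correctly calibrated intervals. By normal approximation, with clustering allowed for, power for an assumed 10-point fall from an assumed 49% is about 48% (75 per cluster) and 51% (91.7 per cluster). The chi-square would hide that limit on precision but would not remove it.

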**Sample size and design for Baseline and End line Surveys**

Clearly it would be impossible to conduct an in-depth evaluation of all population in the community based nutrition program. However, the assessment must be robust, scientifically valid and plausible within existing time frames. Therefore a representative sample size has been calculated separately for both baseline & endline surveys and embedded Randomized control trial. Details of both estimations are as under:

Below mentioned formula for sample size estimation for baseline and endline cross sectional surveys were used from MI & CDC manual [6] to calculate the sample size. Prevalence of stunting (49% Sindh) from NNS 2011, 80% power to detect 10% reduction in prevalence of stunting during the three-year implementation of the Stunting Prevention Programme with a significance level of 0.05 was considered for sample size estimation.

[figure not shown]

Assumptions:

- p1 is stunting rate at baseline without intervention at baseline survey =49%
- p2 is estimated stunting rate after intervention at end line survey
- DEFF : The estimated design effect = 1.5
- α : Level of significance (“alpha”), usually 0.05 or 5% (corresponds with 95% confidence interval)
- 1- β: Power, usually 0.8 (80%) Assumed 10% reduction in stunting

For estimating impact of the interventions each group will require 3200 participants. To account for dropouts and data errors, the sample size will increased by 10% giving a new total of 7040 study participants (3520 participants per group). Information will be collected from 4,200 households at baseline and at endline. The study participants from selected households will be pregnant women, lactating women and children under five years. Two stage cluster sampling technique will be used. LHW catchment areas of 29 UCs will be treated as a cluster for intervention group and control group.

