**Recruitment of potential participants:**

Children 6-23 and 24-59 months of age and Pregnant or lactating mothers will be potentially eligible cohorts for inclusion in the study and will be identified through the baseline survey being done in the targeted union councils. Pregnant women will be enrolled during first and second trimester of pregnancy, children 6-23 months cohort during 6-18 months and children 24-59 months cohort during 24-54 months of age for minimum exposure of six months. A detailed recruitment form will be filled from each study participant. Detailed physical & anthropometric examination and sport Hb testing will also be done at the time of recruitment.

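### The trial measures height-for-age at recruitment in two child cohorts, but the protocol does not commit the primary stunting comparison to adjusting for it

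*Protocol*

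**What the plan says.** The Primary Outcome Measure section of the protocol reads: "The primary outcome will be reduction in risk of stunting in intervention group compared with control group". It names no test.

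The Data Analysis section belongs to the part on the nested CRT. It mentions univariate and multivariate methods in general, a Pearson chi-square test for association between categorical variables, and agreed dummy tables. For the growth outcomes it says: "Bivariate analysis will be done to establish association with the various factors and growth parameters such as stunting, wasting and underweight". No regression model, covariate or recruitment value is named.

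Under Recruitment of potential participants, children enter at 6-18 months or 24-54 months, and "Detailed physical & anthropometric examination and sport Hb testing will also be done at the time of recruitment". The Quarterly Surveillance section repeats the anthropometry every three months. The Secondary Outcome Measures already include HAZ increment per month and mean change in weight-for-height z-score.

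**The concern.** A child recruited at 6-18 or 24-54 months may already be stunted, and the eligibility section takes children regardless of nutritional status. The planned minimum exposure is six months. Stunting at follow-up will therefore partly reflect where each child started, and the trial will have measured that starting point.

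The two kinds of analysis that the section ties to categorical or growth outcomes, chi-square and bivariate, cannot use it. The general reference to multivariate methods could cover an adjusted model, but does not tie the primary comparison to one. At stake is precision in a trial with only 6 UCs per arm. There is also the risk that adjusted or unadjusted results are chosen after the recruitment values have been seen.

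**Working it through.** **Inputs**
- Children 6-23 months: "A sample size of 70-75 children per cluster was estimated with a statistical significance of 0.05, power of 0.80, and an intra-cluster correlation of 0.02"; planned enrolment is 900.
- Children 24-59 months: "a sample size of 90-95 children per cluster was drawn, with a statistical significance of 0.05, power of 0.80, and an intracluster correlation of 0.02"; 1100 in total.
- 12 UCs, 6 per arm.
- Effect: "Sample size for children aged 6-23 months was calculated to detect a 10% difference in risk reduction in stunting". Absolute or relative is not stated; both are tried.
- Control rate: none is given for the CRT. The survey calculation is borrowed: "p1 is stunting rate at baseline without intervention at baseline survey =49" (per cent). This is an assumption.
- Two-sided test: an assumption.
- Correlation between recruitment and endline HAZ: not in the protocol, so a range is assumed.

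**1. The plan's own figure.** For 49% v 39% the pooled two-proportion formula gives 386 per arm. The design effect is 1 + (m − 1) × 0.02.
- m = 70: 386 × 2.38 = 919 per arm. m = 75: 386 × 2.48 = 957 per arm. The total is 1837-1915, against 900 stated.
- m = 90: 386 × 2.78 = 1073 per arm. m = 95: 386 × 2.88 = 1112 per arm. The total is 2146-2223, against 1100 stated.

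The stated totals do not reproduce. They lie close to what one arm needs.

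**2. Power without adjustment**, comparing 12 UC means on 10 df, m = 75:
- SE = √[(0.49×0.51 + 0.39×0.61) × 2.48/450] = √[0.4878 × 2.48/450] = 0.0518
- Noncentrality = 0.10/0.0518 = 1.93; power = 41.5% (40.5% at m = 70).
- Children 24-59 months: 44-44.5%.
- With unlimited children per UC, still only about 61%.

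**3. Spread at recruitment.** The SD of the chance difference in stunting between arms is √(2 × 0.2499 × 2.48/450) = 5.2 points. A difference of 5 points or more has probability of about 34%.

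**4. Where adjustment can act.** The variance factor 2.48 is 0.98 within UCs plus 75 × 0.02 = 1.50 between UCs. The between-UC part is 1.50/2.48 = 60%. Removing all within-UC variance and none between UCs would give at most about 61% power. The UC-level correlation therefore matters most.

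**5. Power with adjustment.** Simulation with 3000 runs per row: latent HAZ, 12 × 75 children, t-test on UC means of stunting residuals after regression on recruitment HAZ.

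| Correlation, child level | Correlation, UC level | Unadjusted | Adjusted |
|---|---|---|---|
| 0.7 | 0.3 | 43% | 45% |
| 0.8 | 0.3 | 41% | 44% |
| 0.8 | 0.5 | 44% | 55% |
| 0.6 | 0.6 | 42% | 55% |
| 0.7 | 0.7 | 40% | 61% |
| 0.8 | 0.8 | 40% | 73% |

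Simulation error is about √(0.25/3000) = 0.9 points per entry. Reaching 80% needs about 62% of the variance removed at both levels. Simulated power passed 80% only at stronger correlations: 87% at 0.9 for both levels, and 87% at 0.8 (child) with 0.95 (UC). Nothing in the protocol supports values that high.

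**6. If the 10% is relative** (49% v 44.1%): SE = √[(0.2499 + 0.2465) × 2.48/450] = 0.0523, noncentrality 0.049/0.0523 = 0.94, power about 14%. With 23-50% of the variance removed at both levels, power is 16-22%.

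**The case against.** The strongest objection is that covariates of the primary model usually belong in the statistical analysis plan, which is not shown. The section allows multivariate methods, refers to dummy tables, and never mentions trial arms. Its bivariate sentence can be read as an analysis of associated factors. A reader might infer that the protocol prescribes an unadjusted primary comparison; the text does not say that. What remains is narrower. The only analysis text in the CRT part names methods that cannot carry a recruitment value, and nothing there commits the primary comparison to it.

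Three further objections also stand in part.
- A reader might take the upper end of the power range as the expected gain. It requires HAZ correlations of 0.6-0.8 that hold equally between UCs, and the protocol gives no correlation. With 0.3 between UCs the gain is only 2-3 points.
- A reader might count the 5.2-point spread at recruitment as a bias or a second harm. It is ordinary sampling variation under randomisation and is already inside the 41%. It shows why adjustment helps, and no more.
- The 41% belongs to a UC-level t-test, which the section does not describe. An individual chi-square on 450 v 450 would show a nominal 86%, but it ignores clustering and is not valid here.

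The protocol also already plans a within-child outcome in HAZ increment per month. That is secondary and leaves the primary comparison as it is.

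**Conclusion.** The point holds as a recommendation to commit the primary comparison to the recruitment value in the two child cohorts. Adjustment raised power in every scenario examined and needs no new data. On an absolute reading of the 10%, with 49% borrowed from the survey calculation, a two-sided 5% test, 75 children per UC and ICC 0.02, power goes from about 41% to about 44-73%. On a relative reading it goes from about 14% to 16-22%. The direction is secure; the size is assumed.

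Two limits apply. The adjustment cannot cover every child in the trial, because infants born to enrolled women have no HAZ at recruitment. Nor does it restore the stated 80% power, which 12 UCs do not deliver anywhere in these ranges. That shortfall, and the absence of clustering from the named analysis, are separate problems that need their own answers.

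**What to change.** Add to the Data Analysis section that, in the 6-23 and 24-59 month cohorts, the primary CRT comparison of stunting is adjusted for recruitment HAZ, age and sex within an analysis that accounts for clustering by UC. With 6 UCs per arm, one workable form is a two-stage analysis: regress stunting on these covariates without arm, then compare the 12 UC mean residuals by a t-test on 10 df.

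Name endline HAZ adjusted for recruitment HAZ as the supporting analysis, and adjust child haemoglobin for its recruitment value in the same way. State that infants born to enrolled women are outside this adjustment. Fix the wording before outcome data by arm are seen.

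The cost is wording only, since the measurements are already planned. Any power figure quoted for the adjusted analysis should state its assumed correlations at child and UC level and whether the 10% is absolute or relative.
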